### Study protocol

Subjects will complete a questionnaire that contains six standard demographic questions and ten questions regarding their medical history. Each subject will be randomized to participate in two learning methods of a preclinical seminar within the same topic, in the order of face-to-face and then videoconference or vice versa under open-label conditions. For the study measurements, there will be two subjects and two investigators in every seminar. One investigator will monitor one study participant for the whole period of the measurement. One participant will start with the traditional face-to-face learning, while the other participant will start with video conference method. Regarding the randomization, we will be using tossing a coin method as a simple randomization. The coin will be tossed by the researcher and the participant will guess the result as “head” or “tail”. Heterogeneity of population will be subsided since we use each participant as its own control by applying a randomized crossover sequence of experimental seminar phases. During the learning session, the subjects will interact only with the instructor. The investigators will interact with the subjects only to attach the electrodes and transducer and give signal when to change learning settings. Throughout the learning sessions, the participant will interact with the same instructor within the same learning topic. Repeating students will not be enrolled in this study. The student who already joined the study measurement will not be included for another measurement.

All measurements will be performed in a temperature and humidity-controlled environment. Measurement time per subject will last around 100 min. This includes measurement at baseline, during seminar settings, and a 10-minute break between settings. The measurements will take place at the same time of day. The study flow is depicted in Figure 1.

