### Statistical analysis plan

The primary endpoint constitutes a group difference in Standard Deviation of all NN intervals (SDNN). Further endpoints encompass a change of remainder functional parameters of the ANS. The study is conceptualized as a pilot study due to lack of preliminary work. Because of the exploratory nature of this study and absent preliminary research using the same assessment techniques we did not undertake a formal sample size calculation. We intend to allocate 48 subjects (*n* = 48) as targeted sample size.

All statistical calculations will be performed using GraphPad Inplot, ISI software and PRISM Version 5.01 (Graphpad Holdings, LLC, CA, USA). Normality will be assessed by descriptive and analytic methods (Shapiro–Wilk test). Under crossover conditions randomization with a two-period, two-treatment design (2 × 2 design) will be performed. In addition, carryover effects between treatments and periods will be tested using two-way repeated measures ANOVA (mixed model). A two-sided *p* > .05 indicates no carryover effects due to sequencing order. Measured values at each treatment period will then be normalized by mean measured values at baseline. Data include HRV parameters (RMSSD, SDNN, VLF, HF, LF, LF/HF, total power), sudomotor parameters (SCL, SSR), neurovascular function parameters (Δt50%down, Δt50%up, VCR), and pupil dynamics (resting pupil diameter, pupil light reflex amplitude and latency, recovery time, NPi). Between-group differences (baseline vs face-to-face vs videoconference) will be determined using one-way analysis of variance ANOVA followed by Student–Newman–Keul test. Not normally distributed data will be analysed either after log-transformation or *via* non-parametric Friedman two-way ANOVA approach. The significance level is set to alpha = 0.05 and two-sided *p* < .05 is considered significant.

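### The only rank test named for non-normal data is a Friedman test that, in context, ranks baseline with the two settings and has no period term, so it does not isolate the randomised face-to-face versus videoconference contrast

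*Protocol article*

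**What the plan says.** The Statistical analysis plan section states the comparison first: "Between-group differences (baseline vs face-to-face vs videoconference) will be determined using one-way analysis of variance ANOVA", followed by Student–Newman–Keuls. The next sentence covers departures from normality: "Not normally distributed data will be analysed either after log-transformation or" by a "non-parametric Friedman two-way ANOVA approach". That sentence does not restate the levels and names no follow-up test. The three conditions just listed are the only repeated conditions defined, so they are what Friedman would rank.

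The same section describes the design: "Under crossover conditions randomization with a two-period, two-treatment design". Periods enter the analysis only through a separate carryover test, not through the comparison of settings. Seminar values are first normalised by the mean baseline value. The target is 48 students with two-sided alpha 0.05, and no effect size, standard deviation or power is stated. The Study protocol section says how each pair is split: "One participant will start with the traditional face-to-face learning, while the other participant will start with video conference method".

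**The concern.** The randomised question is face-to-face against videoconference. Baseline is not randomised: it is a short resting recording taken before either session. A three-level rank test mixes the two comparisons.

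- Its overall p-value can be significant only because rest differs from seminar.
- A pairwise comparison taken from the three-level ranks depends on where baseline falls. The face-to-face minus videoconference rank distance is 2 if that student's baseline lies between the two sessions and 1 otherwise.
- Friedman cannot remove a shift between the first and second session. Such a shift is plausible, with two 40-minute sessions on one topic, ten minutes apart.
- Normalising by baseline does not help. Dividing a student's three values by the same positive number leaves their ranks unchanged.

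For any outcome sent down the rank route, possibly including the primary endpoint SDNN, a significant result may say nothing about the settings, or a real difference between them may be missed.

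**Working it through.** The plan has no figure to reproduce, because 48 is declared rather than derived. The first two steps are algebra. The third rests on assumed effects.

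**1. Overall test, limiting case.** Suppose all 48 baselines lie below both sessions and the settings are identical. The expected rank sums are 48 for baseline and 48 × 2.5 = 120 for each setting. With k = 3,

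Q = 12/[nk(k+1)] × ΣS² − 3n(k+1) = (12/576) × (48² + 120² + 120²) − 576 = 648 − 576 = 72,

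against a 5% critical value of 5.99 on 2 degrees of freedom. The test rejects although the settings do not differ.

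**2. Pairwise contrast, same limiting case.** The conventional variance of the rank distance per student is k(k+1)/6 = 3 × 4/6 = 2. It assumes that all three conditions are exchangeable: distance ±1 with probability 2/3 and ±2 with probability 1/3, so 2/3 × 1 + 1/3 × 4 = 2. If baseline lies outside both sessions, every distance is ±1 and the true variance is 1. The standard error is then √2 = 1.41 times too large. A nominal 5% test has size 2P(Z > 1.96 × 1.41) = 2P(Z > 2.77) = 0.56%.

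**3. Intermediate cases by simulation.** Assumptions, none of them in the article:

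- 48 students, 24 per sequence, lognormal outcome;
- between-student log SD 0.35, within-student log SD 0.15 or 0.25 (the ranges below span these two);
- a setting effect of about 0.41 SD of the within-student difference, which gives a paired t-test on logs 80% power.

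Power with no period effect:

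| Baseline shift (log units) | Friedman pairwise, unadjusted | Rank-sum on period differences |
|---|---|---|
| 0 | 66% | 77–78% |
| 0.2 | 55–61% | 77–78% |
| 0.35 | 40–54% | 77–78% |
| 0.6 | 30–38% | 77–78% |

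With no true difference between settings, the pairwise contrast rejects in 4.1–4.6% of trials at no shift, 1.2–2.2% at a shift of 0.35 and 0.6–0.9% at 0.6.

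The overall Friedman test rejects in 5.2–5.8% when all three levels are equal. With the settings identical and a baseline shift of 0.2 to 0.6, it rejects in 87–100% across repeat runs.

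At a baseline shift of 0.35, a period effect of 0.5 SD of the differences lowers the pairwise power to 29–45%, and one of 1 SD lowers it to 11–24%. The rank-sum test on period differences is unaffected. In a separate run with period effects of 0, 0.5 and 1 SD it kept 76–78% power, with size 4–6%.

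**The case against.** A reader might infer that Friedman gives wrong error bars in general, or is invalid here. The article does not support that. Friedman ranks within each student and so respects the pairing, and its overall size is about 5% when the three levels are equal. If every pair is complete the sequences are 24:24. A period effect then adds noise to the setting contrast rather than bias, and the pairwise comparison errs on the conservative side. Treating the three conditions as independent groups is a fault of the one-way ANOVA, not of Friedman.

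Four further points have force.

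- **No post-hoc test is named after Friedman.** The pairwise power figures apply only if a conventional contrast is used. A signed-rank follow-up would avoid the variance problem. It would still ignore period: in the separate run its power was 78% with no period effect, 68–70% at 0.5 SD and 42–43% at 1 SD.
- **Log-transformation is offered on equal terms**, and it fully normalises the lognormal data simulated here. The point therefore matters only for outcomes that actually go to the rank test.
- **The large losses need an assumed baseline shift or period effect.** Without either, the loss is about 11–12 points (66% against 77–78%). The study is an exploratory pilot with no stated power to contradict.
- **The structure comes from the main comparison sentence**, and Friedman inherits it.

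All four limit the size of the point. None makes the three-level test answer the randomised question. The last is a reason to amend both sentences. The article also does not say which quantity is tested for normality, so it cannot be faulted for using raw values.

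**Conclusion.** The point holds in a limited form. Where the rank route is taken, the named test does not isolate face-to-face versus videoconference and does not adjust for period. That the overall test responds to a baseline difference alone follows from its construction. A resting baseline that differs from an interactive seminar with repeated deep breathing is to be expected, but how far it differs is not known from the article.

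The loss of power is conditional. It applies to a conventional Friedman pairwise contrast that the article does not specify, and its size (from 66% down to about 30%, lower still with a period effect) depends on the assumptions listed. It should not be read as the expected power of this trial. The change is an inexpensive improvement for a pilot, not the repair of an invalid analysis.

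**What to change.** Amend the non-normal-data sentence in the Statistical analysis plan section as follows.

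- Where the rank route is used, compare the settings by a Wilcoxon rank-sum test of each student's period difference (session 1 minus session 2) between the two sequences.
- Report a Hodges-Lehmann estimate with 95% confidence interval for face-to-face minus videoconference. The period difference contains plus the setting effect in one sequence and minus it in the other, so the shift between sequences is twice the setting effect and must be halved.
- Keep baseline out of this test and report baseline against each setting separately, for example by signed-rank test.
- State that normality for this contrast is judged on the within-student differences.

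Make the matching correction in the main ANOVA sentence: a within-student comparison of the two settings with period in the model, and baseline reported apart. The cost is a few sentences, with no new data and no extra students.

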### Data management

The personal data collected in this study will be treated confidentially in accordance with data law, protected from access by unauthorised third parties and may only be published by the executing institutions in anonymized form after the subjects have given their written consent. Anonymity is guaranteed by assigning a student number. Personal data are encrypted in the test forms; only subject numbers are noted in them. Recorded data from measurements will be encrypted as well and kept with labelled subject number. This document will be kept separately from personal data.

### Informed consent

The investigator will obtain informed consent of a subject prior to any study-related procedure. The study protocol will be explained in detail to the subjects by the investigators. In addition, each subject will receive detailed study information in writing. After all questions have been answered, the subject will sign the written informed consent form. One original copy of the written informed consent will be kept in the study centre and a second original copy will be handed out to the subject.

### Limitations and strengths

This study is limited by its pilot nature. However, the detailed autonomic nervous system phenotyping as well as the randomised crossover design ensure high internal validity. Moreover, the results of this study may help to elucidate how the digital transformation of learning in medicine affects psychophysiological health and form a basis for research in large populations of medical learners to identify most effective learning strategies that utilize digital communication and learning tools. Since this is an exploratory pilot study, we will not undertake any validation study prior to the use of the learning progress test. The test will be designed by the lecturers participating in our study based on their expertise in the field. However, the crossover design of our study will ensure comparability of cohorts as each subject will be their own control. This will also minimize inter-individual variability as well as confounding by factors that affect the physiologic and learning responses of the learners to achieve high internal validity.

## Data Availability

N/A (Study Characteristics, no data reported)
